### Eligibility criteria

#### Inclusion criteria

Neonates with a prenatally or postnatally confirmed diagnosis of CCHD requiring (anticipated) cardiac surgery with CBP within the first 4 weeks of life are eligible for inclusion. This includes neonates with the following cardiac defects: (1) transposition of the great arteries with or without a ventricular septal defect undergoing arterial switch operation with ventricular septal defect closure if needed; (2) univentricular hearts—hypoplastic left and right heart syndrome or variant undergoing Norwood stage I or Sano palliation; (3) aortic arch anomalies—interrupted, hypoplastic aortic arch, and/or coarctation of the aorta with or without intracardiac defects (ventricular/atrial septal defect or (sub)aortic stenosis) who undergo complete biventricular repair and/or aortic arch repair; and (4) other variants—truncus arteriosus, total anomalous pulmonary venous connection, or tetralogy of Fallot. Written informed consent of both parents is required prior to inclusion.

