#### Randomization and allocation concealment

Randomization will be performed by Ace Pharmaceuticals in blocking for both the prenatal and postnatal diagnosis group (by Randlist version 1.2 software). Stratification will be conducted per center and for a prenatal diagnosis or postnatal diagnosis of CCHD. The first available box of blinded study medication will be allocated by the study team to consecutive study subjects. Each box will be labeled with a unique medication identification number, which enables identification of treatment allocation for data analyses afterwards or emergency unblinding.

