#### Secondary analysis

Secondary analysis is based on the comparisons of secondary outcomes between the allopurinol and mannitol-placebo group, both for the total study population and separately for subgroups of CCHD. Additionally, a secondary analysis will be performed to assess an interaction with gender, as females possibly benefit more from allopurinol administration than males [30]. Descriptive statistics will be applied, including the independent sample *t*-test or the Mann-Whitney *U*-test for continuous data and Pearson’s chi-square test for categorical data. Safety analyses will be based on incidences of (serious) adverse events in both groups.

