### Data management and monitoring

Senior data managers from the UMC Utrecht (sponsor) will supervise and assist data management during the trial. A data management system (Castor Electronic Data Capture) will be used to enter relevant data of each participant in electronic case report forms (eCRFs). These forms are created by the study team and include items on baseline, study medication, imaging, adverse events, clinical characteristics, and all primary and secondary outcomes. In the eCRFs, the participants will be pseudonymized and presented with their study identification number and allocation number. Castor Electronic Data Capture complies fully with Good Clinical Practice guidelines; the data will be traceable from logging in to data modification. The electronic database is secured through role-based access: only the study team will have access to the database, after permission from the principal investigator. Complex validation rules in the CRF are available to ensure that the collected data is complete, consistent, and correct. Additionally, we built in range checks for data values to promote data quality. Source data will be stored securely in each participating center. The imaging data will be shared via the Research Digital Imaging and Communications in Medicine server of the sponsor. An independent monitor will perform routine inspections at each study site to secure study integrity and quality of data. The case report forms and futher details on data management procedures are available upon request from the corresponding author.

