## Discussion

The CRUCIAL trial focuses on the neuro- and cardioprotective effects of allopurinol administration early after birth and around cardiac surgery with CPB in neonates with CCHD. We aim to provide definite answers on allopurinol’s immediate effects on brain injury and cardiac function, as well as late effects on neurodevelopment. If allopurinol proves to be beneficial in limiting parenchymal brain injury, our subsequent goal is to make allopurinol clinically available for all CCHD neonates.

Large randomized controlled trials that include both structural brain imaging with MRI and long-term follow-up are needed to investigate the effects of neuroprotective drugs in CCHD neonates. A phase III, randomized, quadruple-blinded, placebo-controlled, multicenter study is the most adequate design to prove the efficacy or futility of allopurinol as a neuroprotective agent in the CCHD population. A phase III study seems justifiable since previous studies have already suggested neurocardiac protective effects of allopurinol without serious side effects [24–26]. Multiple pediatric heart centers should be involved to include our anticipated sample size of CCHD neonates considering the relatively low prevalence of CCHD and the heterogeneity of cardiac defects [1]. An interim analysis halfway with the option to stop for efficacy or futility ensures that allopurinol is not unethically withheld or unnecessary given to subsequent CCHD neonates [61].

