We chose to include brain injury on postoperative MRI in the composite primary outcome instead of neurodevelopmental outcome at the age of 24 months. Firstly, neonatal MRI can be used as a “bridging biomarker” for long-term outcomes since ischemic white matter lesions are known to be associated with lower intelligence quotient and attention problems at school-age, and in case of posterior limb internal capsule involvement, also motor problems [36]. Consequently, the beneficial effects of allopurinol on parenchymal brain lesions are expected to improve long-term neurodevelopmental outcomes. Furthermore, early neurodevelopmental outcome at the age of 24 months seems less predictive for long-term outcomes, since CCHD neonates “grow into their deficits” and neurodevelopmental problems become more apparent at school-age [4]. Moreover, CCHD neonates with a syndromic disorder (approximately 15%) can be included as well by assessing brain injury postoperatively on MRI (as part of the composite primary outcome) instead of neurodevelopmental outcome at the age of 24 months. This syndromic CCHD subgroup is expected to score lower on neurodevelopmental outcomes and, therefore, will be analyzed separately [58]. Lastly, as many CCHD neonates undergo multi-staged cardiac repair through infancy, neurodevelopmental outcomes may exhibit a collective effect from multiple surgeries.

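### Continuous secondary outcomes, including the 24-month Bayley scores, are compared by unadjusted two-sample tests, although cardiac-defect group and the randomisation strata could be adjusted for; the cost is some precision, of unknown size.

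*Protocol article*

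**What the plan says.** The Secondary analysis section of the protocol article sets out how the arms are compared on secondary outcomes: "Descriptive statistics will be applied, including the independent sample" t-test or the Mann-Whitney test for continuous data. The comparisons are made "both for the total study population and separately for subgroups of CCHD". No adjusted model is named for any outcome. The continuous outcomes in Table 1 include the motor optimality score, the Bayley-III-NL composites, quality of life, NIRS and echocardiographic measures.

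The Inclusion criteria list four defect groups. One is "hypoplastic left and right heart syndrome or variant undergoing Norwood stage I or Sano palliation"; another is transposition treated by arterial switch. Randomisation does not use defect: "Stratification will be conducted per center and for a prenatal diagnosis or postnatal diagnosis of CCHD".

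The Discussion refers to "the heterogeneity of cardiac defects" and also says that "as many CCHD neonates undergo multi-staged cardiac repair through infancy, neurodevelopmental outcomes may exhibit a collective effect from multiple surgeries". According to Data management and monitoring, the case report forms "include items on baseline, study medication, imaging, adverse events, clinical characteristics, and all primary and secondary outcomes".

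**The concern.** Defect group is part of eligibility, cannot be changed by treatment, and is needed for any analysis by type of heart defect. An unadjusted test on the whole population leaves all variation between defect groups in the error term. Randomisation balances defect in expectation, but in one trial of this size the arms can differ by chance in their share of univentricular infants.

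The same holds for centre and prenatal or postnatal diagnosis. They are used to stratify the randomisation, and a test that then leaves them out has a standard error somewhat too large to the extent that they are prognostic.

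Separate subgroup comparisons do not help here. Each uses only part of the sample, and none makes the overall comparison more precise.

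Better neurodevelopment is one of the trial's stated aims, and the Sample size section gives power for the primary endpoint only. The Bayley difference is also the denominator of the cost-effectiveness ratio, so imprecision in it carries into that ratio.

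**Working it through.** **1. The plan's own figure.** The only stated power is about 80% for the primary composite with 236 infants (188 prenatal, 48 postnatal).
- Control: (188 × 0.71 + 48 × 0.55)/236 = 67.7%.
- Allopurinol: (188 × 0.51 + 48 × 0.46)/236 = 50.0%.
- With 118 per arm and two-sided 5%, the power is 79.6%. The figure reproduces, and the present point does not touch it.

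**2. Unadjusted Bayley comparison.** Inputs: SD 15 (the norm SD in Neurodevelopmental follow-up) and 118 per arm.
- SE = 15 × √(2/118) = 1.95 points.
- Difference detectable with 80% power = 2.80 × 1.95 = 5.47 points.
- Syndromic children (about 15%, Discussion) are analysed separately. That leaves 236 × 0.85 ≈ 200, or about 100 per arm before deaths and losses. The SE is then 15 × √(2/100) = 2.12 and the detectable difference 5.94 points.

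**3. Gain from adjusting for defect.** If defect explains a share R² of the variance, the residual SD is 15 × √(1 − R²). For an effect with 80% power unadjusted, power becomes Φ(2.80/√(1 − R²) − 1.96), whatever the sample size or SD. R² is an assumption.

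| R² (assumed) | SE, 118 per arm | Detectable difference | Power | Equivalent extra children, 1/(1 − R²) − 1 |
|---|---|---|---|---|
| 0 | 1.95 | 5.47 | 80% | 0% |
| 2% | 1.93 | 5.42 | 80.8% | 2% |
| 5% | 1.90 | 5.33 | 82.0% | 5% |
| 10% | 1.85 | 5.19 | 84.0% | 11% |
| 20% | 1.75 | 4.89 | 87.9% | 25% |

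**4. What R² might be.** Take a univentricular share p and a gap of g points to all other infants, with total SD 15. Then R² = p(1 − p)g²/225. Neither p nor g is in the document.
- p = 20–30%, g = 3–5: 0.16 × 9/225 = 0.6% up to 0.21 × 25/225 = 2.3%.
- p = 20–30%, g = 7.5–15: 0.16 × 56.25/225 = 4% up to 0.21 × 225/225 = 21%.
- Four groups with assumed shares 35/20/35/10%, two groups 3 points below the best, and univentricular infants 7.5 or 15 points below: R² is about 3% or 13%.

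**5. Chance imbalance.** With 100 per arm, the SD of the difference in univentricular share is √(2p(1 − p)/100) = 0.057–0.065. At the 95% limit that is 11–13 percentage points. With g = 7.5–15 it moves the unadjusted difference by 0.8–1.9 points, against an SE of 2.12.

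This is not a second benefit on top of step 3. The variance from imbalance is 2p(1 − p)g²/100, which equals R² × 2 × 225/100, exactly the part of the squared SE that adjustment removes. For p = 30% and g = 15 both are 0.945, out of 4.5.

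**6. Price.** Four defect groups need three parameters. Because defect is balanced only by chance, they inflate the variance of the arm difference by roughly 3/200 = 1.5% on average. At R² = 2% this uses up most of the gain; at 10% it is small beside it. Step 3 does not deduct it.

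**The case against.** The strongest reply is that the document never shows defect to be strongly prognostic. The Discussion says only that multiple operations may have a collective effect on neurodevelopment, as a reason for not making the 24-month outcome primary. It mentions heterogeneity of defects as a reason for recruiting in several centres. No score gap, ranking or R² is given, and at an R² of about 2% nothing useful is gained. This stands: plausibly prognostic is as far as the text goes.

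It also stands that the plan does not ignore defect. It foresees analyses by CCHD subgroup, though without defining the subgroups, and it analyses syndromic children, who are expected to score lower, separately.

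A third reply is that the list of tests is open-ended and that covariates for secondary outcomes are normally left to a statistical analysis plan. This stands only in part. Silence would be no finding, but the protocol names unadjusted tests. A model added elsewhere would sit beside them with nothing to say which governs.

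Finally, a proportional-odds model in place of the Mann-Whitney test would add an assumption and change the effect measure, while Table 1 reports means or medians. That is fair, and the fix does not ask for it.

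**Conclusion.** The point holds as one of lost precision in secondary outcomes. A reader might infer that the unadjusted comparisons are biased or invalid, or that a strong predictor is being disregarded. The document supports neither. The tests are valid under randomisation, the type I error, primary analysis and sample size are untouched, and the strength of the association is not stated.

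For the Bayley score, adjustment would raise 80% power to between about 81% and 88% over an assumed R² of 2% to 20%, before the small price of the extra parameters. The points figures rest on the norm SD of 15; the power figures rest on R² alone. The same relation applies to other roughly normal outcomes, but there is no basis for an R² for any of them. The effect of adding centre and prenatal or postnatal diagnosis cannot be sized from the document either.

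The change is worth making because it costs little if defect is weakly prognostic and gains materially if it is not.

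**What to change.** In the Secondary analysis section, make the main comparison of continuous secondary outcomes a linear model with arm, cardiac-defect group (the four groups of the Inclusion criteria), centre, and prenatal or postnatal diagnosis. Report the adjusted mean difference with its 95% confidence interval, beside the per-arm summaries of Table 1. Keep the t-test or Mann-Whitney test as a sensitivity analysis. For clearly skewed or ordinal scores, the Mann-Whitney or another rank-based test can remain.

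Do not use preoperative MRI or echocardiography as a baseline covariate in the prenatal group. The first two doses are given within about half a day of birth, while these examinations are planned at 4–7 days, so treatment may already have affected them.

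The cost is wording, settled before unblinding, plus a few degrees of freedom: three for defect, up to three for the four centres and one for diagnosis, in about 200 children. No new data should be needed, since eligibility and the planned subgroup analyses already require the defect. The fourth defect group combines several lesions and is a coarse category, which limits what adjustment can recover.

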#### Secondary outcomes

The secondary outcomes that will be compared between the allopurinol and mannitol-placebo groups are presented in Table 1 and include the five elements (domain, specific measurement, specific metric, method of aggregation, and time point) as described by Zarin et al. and Saldanha et al. [55, 56].

**Table 1 Tab1:** Secondary outcomes

Domain	Specific measurement	Specific metric	Method of aggregation	Time point
Brain injury severity	Brain injury severity score, determined by the assessment of brain injury on MRI in the deep gray matter, white matter, cortex, and cerebellum [39, 40].	Preoperative brain injury severity score, postoperative brain injury severity score, and change between pre- and postoperative brain injury severity score	Mean (and SD) or median (and IQR) per group	Preoperative (4–7 days after birth) Postoperative (5–10 days after surgery or at least within 1 month after surgery)
White matter injury volume	White matter injury volume (mm^3^), determined by manual segmentation with 3D-Slicer or ITK-SNAP 2.0 [41–43].	Preoperative white matter injury volume, postoperative white matter injury volume, and change between pre- and postoperative white matter injury volume	Mean (and SD) or median (and IQR) per group	Preoperative (4–7 days after birth) Postoperative (5–10 days after surgery or at least within 1 month after surgery)
Echocardiographic systolic and diastolic function	Echocardiographic assessment of global ventricular function (normal, mildly reduced, moderately reduced, severely reduced); ejection fraction (%); shortening fraction (%); ventricular dimensions (mm, *Z*-score corrected for BMI); velocity over the cardiac valves, i.e., *V*peak (m/s) and *V*mean (m/s); cardiac valve insufficiency (no, mild, moderate, severe); longitudinal strain (%) and tissue Doppler imaging (myocardial deformation indices (m/s)); and systolic and diastolic pulmonic vein flow (m/s) [44].	Preoperative echocardiographic measurements, postoperative echocardiographic measurements, and change between pre- and postoperative echocardiographic measurements	Distribution per group for categorical variables and mean (and SD) or median (and IQR) per group for continuous variables	Preoperative (4–7 days after birth) Postoperative (5–10 days after surgery or at least within 1 month after surgery)

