#### Sample size

The sample size is calculated based on an assumed reduction in (absolute) incidence of 20% in the more prevalent subgroup of prenatal diagnosis (± 80% of the total population, control event rate assumed 71%) and a reduction of 9% in the postnatal diagnosis group (± 20% of the population, control event rate assumed 55%). With a total sample size of 236 CCHD neonates, of which 188 in the prenatal subgroup and 48 in the postnatal subgroup, the study has approximately 80% power to demonstrate the advantage of allopurinol in the total group with a two-sided alpha of 5%. The power of the hierarchical testing strategy is only slightly affected, given the large proportion of the prenatal group (80%). The effect sizes are a relevant and viable expectation and are based on the results of previous neuroprotective studies on head cooling in neonatal encephalopathy and perioperative allopurinol administration in CCHD neonates [26, 59]. RStudio version 3.6.1 was used for the sample size analysis.

Participants will be substituted in the following cases: (1) when cardiac surgery with CPB in the first month of life is unexpectedly not required or (2) when there is consent withdrawal before postoperative MRI. It is to be expected that these cases rarely occur.

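### Two ordered four-grade echocardiographic outcomes fall under Pearson's chi-square, which ignores the ordering and gives up power against a consistent shift

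*Protocol article*

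**What the plan says.** Table 1 (Secondary outcomes) lists two echocardiographic items on graded scales: "global ventricular function (normal, mildly reduced, moderately reduced, severely reduced") and "cardiac valve insufficiency (no, mild, moderate, severe"). Its aggregation column gives "Distribution per group for categorical variables" and means or medians for the continuous echocardiographic measures.

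Secondary analysis then ties tests to data types. The t-test or Mann-Whitney test is assigned to continuous outcomes, followed by Pearson's "chi-square test for categorical data". The sentence opens with "Descriptive statistics will be applied, including the independent sample", so the list is not presented as complete, but categorical data do have a named test. The article names no trend test, rank test or ordinal model for graded outcomes.

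**The concern.** Each scale runs in one clinical direction, from normal or absent to severe. Pearson's chi-square on a two-by-four table treats the grades as labels: exchanging the normal and severely reduced columns leaves the p-value unchanged. It spreads its sensitivity over 3 degrees of freedom and does not say which arm did better.

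The Background and Discussion give improved cardiac function as an aim, which is a directional question. For a consistent move towards better grades, a test that uses the order will usually detect more with the same data. At stake is efficiency and clarity of interpretation for two secondary outcomes. Bias is not at issue.

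**Working it through.** **Number per arm.** The Sample size section states: "With a total sample size of 236 CCHD neonates, of which 188 in the prenatal subgroup and 48 in the postnatal subgroup". With equal allocation that is 236/2 = 118 per arm. As a check on this reading, the article's own power figure was reproduced.

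- Control rate: (188 × 0.71 + 48 × 0.55)/236 = 0.6775.
- Allopurinol rate: (188 × 0.51 + 48 × 0.46)/236 = 0.4998.
- Power of a two-sided 5% test with 118 per arm: 79.6%, against the stated 80% or so.

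That figure concerns the primary endpoint. The article states no power for any echocardiographic outcome.

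**Cost of the extra degrees of freedom, without a grade distribution.** A 1-df test with power P at two-sided 5% has noncentrality λ = (1.96 + z_P)². For P = 80%, λ = (1.96 + 0.84)² = 7.85. If the same λ is tested on 3 df (critical value 7.81), power falls to 64.5%. Likewise 60% becomes 43.2%, 70% becomes 53.1% and 90% becomes 78.4%. This is an approximation, since the two statistics need not have exactly the same λ.

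**Simulation.** There were 20,000 trials per setting with 118 per arm. The cumulative odds of a better grade are multiplied by a common odds ratio (OR). Pearson chi-square is compared with the tie-corrected Mann-Whitney test at two-sided 5%. The control distributions (best to worst grade) and the odds ratios are assumptions. As an example, control 50/30/15/5% has cumulative odds 1, 4 and 19. Doubling gives 2, 8 and 38, so the treated grades are 66.7/22.2/8.5/2.6%.

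| Control grades (%) | OR | Chi-square | Mann-Whitney | Loss (points) |
|---|---|---|---|---|
| 40/30/20/10 | 1.5 | 26.3% | 39.5% | 13.2 |
| 40/30/20/10 | 1.8 | 50.5% | 67.9% | 17.4 |
| 40/30/20/10 | 2.0 | 65.4% | 80.7% | 15.3 |
| 40/30/20/10 | 3.0 | 96.9% | 99.2% | 2.3 |
| 50/30/15/5 | 1.5 | 23.8% | 36.5% | 12.7 |
| 50/30/15/5 | 1.8 | 45.7% | 63.3% | 17.6 |
| 50/30/15/5 | 2.0 | 60.4% | 77.0% | 16.6 |
| 50/30/15/5 | 3.0 | 94.8% | 98.5% | 3.7 |
| 70/20/7/3 | 1.5 | 17.0% | 27.7% | 10.7 |
| 70/20/7/3 | 2.0 | 43.2% | 61.1% | 17.9 |
| 70/20/7/3 | 3.0 | 80.9% | 92.2% | 11.3 |

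The loss is largest when the rank test has middling power and shrinks once both tests are near certain. Four equally common grades give a similar pattern, with 1.3 points lost at OR 3. With no effect (OR 1), the rejection rate over all four distributions was 4.5 to 5.1% for chi-square and 4.9 to 5.2% for Mann-Whitney.

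**Where the ordering does not help.** If control 40/30/20/10% became 30/45/20/5%, with the middle gaining from both ends, chi-square would have 61% power and Mann-Whitney 7%.

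**The case against.** Chi-square is valid here. The outcomes are secondary and described as descriptive, they lie outside the hierarchical primary testing, and the trial is not sized for them. Only two items are affected: ejection and shortening fraction, ventricular dimensions, velocities, strain, tissue Doppler and pulmonary vein flow are continuous and go to the t-test or Mann-Whitney test. The direction can be read from the distribution reported per group. Proportional odds is also the pattern that favours a rank test. All of this stands, and it sets the severity. It does not remove the point, because the article names the test and the test does not match a directional aim. A non-monotone shift would not show improved function.

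Two stronger readings are tempting, and the documents support neither.

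- A reader might take a loss of 16 to 18 points as a property of the plan. It is not: the article gives no grade distribution or effect size, and such a loss lies near the top of the range.
- A reader might add that the listed two-group tests cannot test the planned interaction, since "a secondary analysis will be performed to assess an interaction with gender". That is true of those tests taken alone. But the list is open and the interaction is announced as an additional analysis. Nothing says it will be done with a two-group test or by separate tests in each sex. Its model is detail that an article commonly leaves to the analysis plan.

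**Conclusion.** The point holds at low severity. On the article's wording, global ventricular function and valve insufficiency would be tested with a 3-df test that ignores their ordering and gives no direction. Type I error is about 5%, so nothing is invalid and the primary analysis is untouched.

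Under proportional odds ratios of 1.5 to 3, the three skewed control distributions tabulated above and 118 per arm, the loss of power is about 2 to 18 points. It is about 15 to 18 points where the rank test would have roughly 60 to 80% power. These figures rest on assumed grade distributions and a consistent shift; for a non-monotone shift the comparison reverses.

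**What to change.** Add one sentence to Secondary analysis: ordered grades (global ventricular function and valve insufficiency) will be compared with the Mann-Whitney test, or with a proportional-odds model reporting a common odds ratio and confidence interval. Keep Pearson's chi-square for binary and unordered outcomes. Settle the choice before unblinding, so that it cannot depend on the results.

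This needs no further data, and the Mann-Whitney test is already in the plan. The one price is lower sensitivity to a non-monotone shift, which is not the trial's hypothesis and would still be visible in the reported distributions.
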